## Discussion

There is a major unmet need for better evidence-based treatment in sarcoidosis. Although this has already been acknowledged in the ATS/ERS/WASOG guideline 20 years ago, research into first-line treatment options is still lacking. This will be the first study evaluating the efficacy of methotrexate as a first-line treatment for pulmonary sarcoidosis. As prednisone is often accompanied by many side-effects, the possibility to choose for methotrexate as first-line therapy may potentially lead to a reduction in side-effects and improvement in quality of life for patients. A non-inferiority design was chosen since we hypothesize that methotrexate is as effective as prednisone (non-inferiority margin considered), but has fewer side-effects. We chose a non-blinded design because it would be practically impossible to integrate dosing and tapering schedules as described in a double-blind study.

Previous studies evaluated the efficacy of methotrexate as second-line therapy and showed a steroid-sparing effect and significant increase in pulmonary function. In these trials, dosages between 10 and 15 mg methotrexate were used [14, 15]. In the current trial, methotrexate will be initiated at 15 mg and, if tolerated, subsequently increased until 25 mg. This treatment schedule is chosen based on experiences with methotrexate in rheumatoid arthritis, for which starting dosages of 15 mg/week escalating with 5 mg/month to 25-30 mg/week have been demonstrated to have the best clinical efficacy [25]. By using an online home monitoring program, potential side-effects will be closely monitored and where needed medication will be adjusted. The study design and treatment schedule have been developed together with a patient panel, to ensure that the burden of study participation will be acceptable for patients.

Next to side-effects and symptoms, the home monitoring program also allows for close monitoring of lung function. A previous observational study in patients with pulmonary sarcoidosis, newly treated with prednisone, showed that home spirometry can reliably detect changes in pulmonary function in sarcoidosis patients and assess the time to pulmonary improvement [8]. The major increase in FVC already occurred within the first month of treatment; however, until now no consensus exists on the optimal tapering schedule [7]. The PREDMETH trial will also provide data on time to pulmonary improvement in patients treated with methotrexate, which are currently lacking. The online home monitoring program that will be used in the current study, has been previously evaluated together with sarcoidosis patients in a pilot study. This study showed that patient satisfaction and compliance were high, and the reproducibility of FVC was good [21]. Thus, home monitoring will allow us to better evaluate (early) response to therapy, could enable personalized tapering of medication in the future and will provide more insights in the balance of effects and side-effects in newly-treated sarcoidosis patients.

Next to the important clinical aims of the study, the role of serum and cellular biomarkers in disease pathogenesis as well as predicting disease outcome will be further explored [26]. By combining these insights with the clinical outcomes of the study this trial will hopefully provide unique insights in the development and disease course of pulmonary sarcoidosis.

In conclusion, by conducting a randomized clinical trial to compare prednisone and methotrexate as first line treatment of pulmonary sarcoidosis we expect to advance evidence based treatment practice for sarcoidosis. Furthermore, seamlessly integrating translational research on patient samples from this trial will provide more insights not only with regard to tailored treatment, but also in the pathophysiological mechanisms of sarcoidosis. All together, we believe that the proposed study has the potential to enhance evidence-based and personalized therapy that improves outcomes and quality of life for patients with sarcoidosis.

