## Methods/design

### Objectives and endpoints

The main objective of this study is to investigate the effectiveness and tolerability of methotrexate as first-line therapy in patients with pulmonary sarcoidosis compared with prednisone. The primary endpoint of this study is the change in hospital-measured Forced Vital Capacity (FVC) between baseline and 24 weeks. Secondary objectives are to gain more insights in response to therapy in individual patients by home spirometry and patient reported outcomes. Furthermore, we aim to also examine blood biomarkers of disease progression and chronicity, to assess whether response to therapy can be predicted in individual patients, and to gain more insights into the underlying disease mechanism and potential new targets for therapy. Table 1 shows the endpoints of the PREDMETH study.

**Table 1 Tab1:** Endpoints of the PREDMETH study listed as primary endpoint, secondary endpoints and explorative endpoints

Primary endpoint	
- Between-group difference in change in hospital-measured Forced Vital Capacity (FVC) % predicted between baseline and 24 weeks	
Secondary endpoints	

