### Design and participants

The PREDMETH study is a prospective, randomized, non-blinded, multi-center, non-inferiority trial, designed to compare effectiveness and tolerability of methotrexate versus prednisone as first-line therapy for pulmonary sarcoidosis. The study is a joint design of clinicians, scientists and a patient expert panel. In this study, 18 centers in the Netherlands will participate. The study will randomize a total of 138 treatment-naïve adult sarcoidosis patients, about to start first-line therapy for a pulmonary indication.

Patients will be informed about the study by their treating physician. If patients are willing to participate, written informed consent will be obtained, and patients will be screened for eligibility. The in- and exclusion criteria are shown in Table 2. If eligible, patients will be randomized in a 1:1 ratio to receive either prednisone or methotrexate for 24 weeks, after which they will be followed up in regular care up to 2 years. For allocation of each subject to a treatment arm a centralized electronic randomization system will be used. Hospital visits will take place at 4, 16 and 24 weeks, and for long-term follow-up after 1 year and 2 years. Additionally, patients will be asked to perform weekly home spirometry and record symptoms and side-effects via a home monitoring application for 24 weeks.

**Table 2 Tab2:** Inclusion and exclusion criteria

Inclusion criteria	Exclusion criteria

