### Hospital visits

Baseline characteristics of patients, such as gender, age, self-reported ethnicity, smoking status, comorbidity, co-medication, date of sarcoidosis diagnosis, details of organ involvement, and if available details of x-ray and chest CT scan will be recorded. At every visit, a physical examination will be performed to record weight, height, waist circumference and blood pressure of the patients. In-hospital pulmonary function measurements will include FVC, Forced Expiratory Volume in 1 second (FEV1) and diffusion capacity of the lung for carbon monoxide (DLCOc). Furthermore, routine blood samples will be collected to assess blood count, kidney- and liver function. An additional sample of 80 ml blood will be taken for analysis of Angiotensin coverting enzyme (ACE), Serum soluble interleukin-2 receptor (sIL-2R), monocyte subsets, T-cells, dendritic cells, and proteomics biomarker discovery. Patients will also be asked to complete patient-reported outcome measures (PROMs) via a home monitoring app at every visit. The PROMs consist of the Fatigue Assessment Scale (FAS), the King’s Sarcoidosis Questionnaire (KSQ), Global Rating of Change Scale (GRoC), Chronic Respiratory Questionnaire (CRQ), Patient Experience and Satisfaction with Medication Questionnaire (PESaM) and Euroqol-5D-5L questionnaire (EQ-5D-5L). At follow-up visits all adverse events will be evaluated and recorded. Side-effects will be managed according to the discretion of the treating physician. Physicians can deviate from the treatment flowchart at any time, if the clinical situation demands so. The study design is shown in Table 3.

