### Treatment schedule

For prednisone the standard dosage according to literature is 20–40 mg daily [3, 7]. Patients will start with 40 mg prednisone daily for 4 weeks. Subsequently, this dose will be tapered to a maintenance dose of 10 mg/day within 16 weeks. The maintenance dose will be continued until 24 weeks after start of treatment. After 24 weeks, the prednisone is either continued at 10 mg or further reduced at the discretion of the treating physician. According to current clinical recommendations patients will also receive calcium 500 mg /colecalciferol 400 IE per day (6 days per week) and risedronic acid 35 mg once a week. In case of intolerable side-effects of prednisone, the treating physician will start early tapering. If side-effects remain intolerable, prednisone will be discontinued and patients will start on the methotrexate schedule.

For methotrexate, the starting dosage will be 15 mg once a week, with folic acid 5 mg once a week. Subsequently, the dose will be increased to 25 mg/week within 8 weeks if tolerated. After 24 weeks, the dose of methotrexate is either continued or reduced at the discretion of the treating physician. Methotrexate will be discontinued if aspartate aminotransferase (AST) is > 3 times the upper limit of normal. In case of intolerable side-effects of methotrexate the total dose will be divided in twice weekly. If side-effects do not subside, oral methotrexate will be switched to subcutaneous methotrexate in the same dose. If side-effects remain intolerable, dosage of subcutaneous methotrexate will be tapered according to the discretion of the treating physician. If side-effects do not subside, methotrexate will be discontinued and the patient will start on the prednisone schedule. If an absolute FVC decline of ≥10% on in-hospital measurement of FVC is detected, the other treatment arm will be added to the current therapy (i.e. patients on methotrexate will additionally start with the prednisone schedule and patients on prednisone will additionally start with the methotrexate schedule). In this case, patients will be treated with both methotrexate and prednisone and remain in the study. At any time, the treating physician may decide to deviate from this treatment schedule if the clinical situation demands so. Figure 1 shows the treatment schedule of prednisone and methotrexate.

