### Sample size calculation

The power calculation is based on data from a previous observational study with prednisone in newly treated patients with pulmonary sarcoidosis. In this study, the mean increase in FVC with prednisone was 15%, with a standard deviation of 10.5% [8]. In a case series of 50 patients with sarcoidosis treated with methotrexate, treatment effect was in line with the findings for prednisone; 66% of patients had more than 15% improvement in vital capacity after 6 months [24]. We chose a non-inferiority margin of 5%, because FVC measurements show biological variation and thus variation < 5% is not considered clinically relevant. Based on these numbers, using a one-sided test with a power of 80% (β) and a type 1 error of 5% (α), the estimated sample size of this study is 110 patients. To allow for 20% drop-out, we aim to randomize 138 patients.

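### The reason given for an open design does not extend to the operator of the post-randomisation hospital spirometry, for whom no masking is described

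*Protocol article*

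**What the plan says.** Under Design and participants the protocol article states: "The PREDMETH study is a prospective, randomized, non-blinded, multi-center, non-inferiority trial". The Abstract uses the same label, and neither place makes an exception for outcome measurement. The only justification is in the Discussion: "We chose a non-blinded design because it would be practically impossible to integrate dosing and tapering schedules as described in a double-blind study".

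The primary endpoint in Table 1 is "Between-group difference in change in hospital-measured Forced Vital Capacity (FVC) % predicted between baseline and 24 weeks". Hospital visits after randomisation fall at 4, 16 and 24 weeks, then at 1 and 2 years.

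The Treatment schedule section gives the same test a second role: "If an absolute FVC decline of ≥10% on in-hospital measurement of FVC is detected, the other treatment arm will be added to the current therapy". Such patients remain in the study.

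The Hospital visits section lists the lung-function tests. It does not say who performs them or whether that person knows the allocation.

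**The concern.** The justification is narrower than the choice it supports. Regimens that cannot be merged into a double-blind scheme are a good reason for patients and treating physicians to know the drug. They have no bearing on whether a lung-function operator must know it. An open-label trial with a masked assessor is an ordinary design, and nothing in the stated reason rules it out.

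This matters for this particular endpoint. That FVC depends on effort, on coaching and on which manoeuvre is accepted is general knowledge and is not stated in the article. If encouragement or acceptance differed between arms, the estimated difference would shift by that amount relative to the 5-point margin. A larger sample would not correct it. Because the same reading triggers combined treatment, a differential reading could also influence who receives both drugs before week 24.

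**Working it through.** **Does the reason cover the operator?**

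- Reason given (Discussion): the two regimens could not be fitted into a double-blind study. This concerns people who take or prescribe the drug.
- Role at issue: the person conducting hospital spirometry at weeks 4, 16 and 24, who neither takes nor, in that role, prescribes it. The reason does not reach this role.
- Baseline: FVC is one of the eligibility measures in Table 2, and Design and participants places randomisation after screening. Baseline FVC therefore appears to precede allocation, and the point concerns post-randomisation tests only.

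**Inputs (Sample size calculation):** SD 10.5, margin 5, one-sided α 5%, power 80%, 20% drop-out, 1:1 allocation. A true difference of 0 follows from the equal-efficacy hypothesis in the Discussion. SD and margin are both read as points of FVC.

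**Reproducing the plan's figure**

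- n per arm = 2 × (1.645 + 0.842)² × 10.5² / 5² = 54.5, rounded up to 55, so 110 in total, as stated.
- 110 / 0.80 = 137.5, rounded up to 138, as stated.

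**Precision**

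- SE = 10.5 × √(2/55) = 2.00 points.
- 1.645 × 2.00 = 3.29, so non-inferiority is declared if the observed difference (methotrexate minus prednisone) is better than −5 + 3.29 = −1.71.
- A 1-point shift is therefore 0.5 SE, or 20% of the margin.

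**Effect of an assumed net operator bias b** (positive favours methotrexate)

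P(declare non-inferior) = Φ((5 + true difference + b)/SE − 1.645)

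| True difference | b | Calculation | Result |
|---|---|---|---|
| −5 | 0 | Φ(−1.645) | 5.0% false non-inferiority |
| −5 | +1 | Φ(1/2.00 − 1.645) | 12.6% |
| −5 | +2 | Φ(2/2.00 − 1.645) | 25.9% |
| 0 | 0 | Φ(5/2.00 − 1.645) | 80.3% power |
| 0 | −1 | Φ(4/2.00 − 1.645) | 63.8% |
| 0 | −2 | Φ(3/2.00 − 1.645) | 44.2% |

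A noncentral-t calculation agrees within 0.5 percentage points. With all 138 analysed (69 per arm, SE 1.79), false non-inferiority is 13.9% or 29.9% for b = +1 or +2. Power falls from 87.5% to 72.3% or 51.3% for b = −1 or −2. Extra patients do not remove the effect.

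The values of b are assumptions; the document gives no figure for operator bias. The calculation also uses a simple comparison of mean changes, so the SE from the planned repeated-measures model could differ.

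**The case against.** The strongest objection is that this is a condensed article. It does not say who runs the spirometry, what the request form shows, or whether operators know the arm, and the full protocol may already describe masking. That stands in part. A reader might infer that spirometry is fully unblinded, but this would come only from the unqualified label and the silence on masking. What remains is that the article states a design choice and gives a reason that does not cover this part of it.

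Other objections also limit the point:

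- **Direction.** A reader might infer that the hypothesis creates an expectation favouring methotrexate. The hypothesis is equal efficacy, and the article also presents prednisone as the established first choice. It says nothing about what operators at 18 centres believe.
- **Size.** Any shift of half a standard error would move error rates this much in any trial. The arithmetic shows sensitivity and does not show that a net shift of 1 or 2 points is likely.
- **Cross-check.** It is tempting to say that no analysis could reveal such a bias. The trial collects weekly home spirometry for 24 weeks, already modelled by treatment group to assess time to pulmonary improvement, and no hospital operator is described as coaching or selecting those readings. This is a partial check, because patients at home still know their drug.
- **Reach of the remedy.** Masking operators leaves bias from patients' own effort untouched, so it cannot be claimed to restore the error rate to exactly 5%.

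None of these supplies a reason for operators to know the arm.

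**Conclusion.** The point holds as a gap in justification and safeguard. The stated reason for an open design applies to patients and prescribers. It does not apply to the operator of the hospital spirometry at weeks 4, 16 and 24, which supplies the primary endpoint and the add-on trigger.

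For scale, an assumed 1-point net operator bias would take false non-inferiority at the margin from 5% to about 13%, or power from about 80% to 64%, depending on its direction. This rests on the plan's SD and margin, 55 evaluable patients per arm, and a bias whose size and direction the document does not establish.

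The document does not support concluding that operators are known to be unmasked, that the result will be biased towards methotrexate, that baseline FVC is affected, or that the sample size is wrong. The sample size reproduces exactly. The change is worth making because it removes one avoidable source of bias at little cost.

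**What to change.** Keep treatment open-label. Have the existing lung-function operators at weeks 4, 16 and 24 work without knowledge of the arm: leave the allocated drug off the spirometry request, tell operators not to ask, and tell patients not to say. Describe the trial as open-label with masked measurement of the primary endpoint. Report the between-arm difference in home-measured FVC as a supportive check on the hospital result.

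If the full protocol already masks operators, one sentence in the article is enough. If masking is judged infeasible, give the reason.

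The cost is a site instruction, a change to the request form and one supportive analysis of data already collected. Sample size, treatment schedule and visits do not change. The downside is that masking will be imperfect, since some patients will disclose their drug or show visible steroid effects, and bias from patients' own effort will remain.

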## Data Availability

The full protocol and metadata will be available on reasonable request. The endpoints of the PREDMETH study are available on www.clinicaltrials.gov; ID NCT04314193.

## Abbreviations

QoL: Quality of life
DCs: Dendritic cells
FVC: Forced Vital Capacity
KSQ: King’s Sarcoidosis Questionnaire
GRoC: Global Rating of Change scale
CRQ: Chronic Respiratory Questionnaire
EQ-5D-5L: Euroqol-5D-5L questionnaire
MRC: Medical Research Council dyspnea scale
FAS: Fatigue Assessment Scale
PESaM: Patient Experience and Satisfaction with Medication Questionnaire
ACE: Angiotensin coverting enzyme
sIL-2R: Serum soluble interleukin-2 receptor
FEV1: Forced Expiratory Volume in 1 second
DLCOc: Diffusion capacity of the lung for carbon monoxide
PROMs: Patient-reported outcome measures
AST: Aspartate aminotransferase
VAS: Visual analog scale
ITT: Intention-to-Treat
